## Abstract

**Background:**

mHealth has experienced a huge growth during the last decade. It has been presented as a new and promising pathway to increase self-management of health and chronic conditions in several populations. One of the most prolific areas of mHealth has been healthy lifestyles promotion. However, few mobile apps have succeeded in engaging people and ensuring sustained use.

**Objective:**

This paper describes the pilot test protocol of the PReventive Care Infrastructure based on Ubiquitous Sensing (PRECIOUS) project, aimed at validating the PRECIOUS system with end users. This system includes, within a motivational framework, the Bodyguard2 sensor (accelerometer with heart rate monitoring) and the PRECIOUS app.

**Methods:**

This is a pilot experimental study targeting morbidly obese prediabetic patients who will be randomized to three conditions: (1) Group 1 - Control group (Treatment as usual with the endocrinologist and the nurse + Bodyguard2), (2) Group 2 - PRECIOUS system (Bodyguard2 + PRECIOUS app), and (3) Group 3 - PRECIOUS system (Bodyguard2 + PRECIOUS app + Motivational Interviewing). The duration of the study will be 3 months with scheduled follow-up appointments within the scope of the project at Weeks 3, 5, 8, and 12. During the study, several measures related to healthy lifestyles, weight management, and health-related quality of life will be collected to explore the effectiveness of PRECIOUS to foster behavior change, as well as user acceptance, usability, and satisfaction with the solution.

**Results:**

Because of the encouraging results shown in similar scientific work analyzing health apps acceptance in clinical settings, we expect patients to widely accept and express satisfaction with PRECIOUS. We also expect to find acceptable usability of the preventive health solution. The recruitment of the pilot study has concluded with the inclusion of 31 morbidly obese prediabetic patients. Results are expected to be available in mid-2017.

**Conclusions:**

Adopting and maintaining healthy habits may be challenging in people with chronic conditions who usually need regular support to ensure mid/long-term adherence to recommendations and behavior change. Thus, mHealth could become a powerful and efficient tool since it allows continuous communication with users and immediate feedback. The PRECIOUS system is an innovative preventive health care solution aimed at enhancing inner motivation from users to change their lifestyles and adopt healthier habits. PRECIOUS includes ubiquitous sensors and a scientifically grounded app to address three main components of health: physical activity, diet, and stress levels.

**Trial Registration:**

Clinicaltrials.gov NCT02818790; https://clinicaltrials.gov/ct2/show/NCT02818790 (Archived by WebCite at http://www.webcitation.org/6qfzdfMoU)

## Introduction

Information and communication technologies (ICT) applied to health and health care systems have been shown to increase their efficiency, improve quality of life, and unlock innovation in health markets. eHealth has emerged as a rapidly increasing area of promoting health, as well as bringing together end users and health care professionals to foster information exchange and effective communication. It is therefore the key technology for 21st century health care, as analyzed and projected within the European Commission eHealth Action Plan 2012-2020 [1]. The mHealth subdomain promises to bridge the gap between health settings and real-world scenarios [2]. Currently, mobile phones are widely used across developed countries. Their portability, ease of use, and ubiquity make them excellent tools to enhance the self-management of health and specifically chronic conditions.

The World Health Organization has estimated that in 2020 chronic or noncommunicable conditions accounted for 87% of deaths in high-income countries. Only 7% of deaths were attributed to communicable conditions and nutritional deﬁciencies and 6% to injuries [3]. The proportion of deaths worldwide caused by noncommunicable diseases is projected to rise from 59% in 2002 to 69% in 2030 [4]. Chronic diseases have traditionally included cardiovascular disease, diabetes, and asthma or chronic obstructive pulmonary disease. As treatments and survival rates have improved, chronic conditions now also include many varieties of cancer, human immunodeficiency virus and acquired immune deficiency syndrome, mental disorders (eg, depression, schizophrenia, and dementia), and disabilities such as visual impairment and joint disease. Many of these conditions are linked to an ageing society but also to lifestyle choices such as smoking, sexual behaviors, diet, and exercise, as well as to genetic predispositions. What these diseases have in common is their need for a long-term and complex response, coordinated by diﬀerent health professionals with access to the necessary drugs and equipment, and extending into social care.

For these reasons, mHealth is a key element to improving the management of chronic conditions because it includes a huge range of possibilities such as psycho-education, ecological momentary assessments, constant monitoring, reliable biofeedback, immediate tailored feedback, and brief interventions [5-8]. However, ensuring adherence and sustained motivation among users is still a complicated and unresolved problem as users have been frequently shown to lose interest in mHealth solutions resulting in decreased compliance of recommendations in the long run [9].

Health games or specialized motivating apps for mobile phones offer a possible solution to address the motivational factors involved in this problem. Thus, these apps try to bring empowerment, joy, engagement, and to offer a social connection to an otherwise rather dull self-management task [10-12]. As a result, the market for health-related games and apps has exploded in recent years, yielding over 100,000 apps in this area [1,2]. However, the information quality of the content of the apps is merely adequate [9]. In addition to functionality and esthetics, app developers should invest in providing content and quality behavioral tracking features, combined with a solid framework including motivational aspects. It is then recommended that they employ psychological techniques known to be effective in changing relevant behavior patterns and to improve the user experience and foster behavior change. Despite growing development and utilization of apps in research, additional experimental evaluation is required to understand whether the presence of particular content, behavior change techniques, motivational feedback, and so on, is associated with behavior change [9].

The PREventive Care Infrastructure based On Ubiquitous Sensing (PRECIOUS) project is a 7th Framework Programme for Research and Technological Development (FP7) project funded by the European Union and part of the eHealth and Ageing Initiative. Given increasing global obesity rates and physical inactivity, the project aims at preventing diseases such as type 2 diabetes and cardiovascular diseases by promoting healthier lifestyles. The project partners have designed and created a fully personalized system able to adapt to the user’s goals and preferences, combined with sensors (Bodyguard2, which is an accelerometer with 24h heart rate monitoring). Food intake, physical activity, stress levels, and sleep patterns are assessed in order to create a complete model of the user’s status called Virtual Individual Model, and subsequently certain measures and possibilities are suggested. A mobile phone‒based client app then finally delivers these interventions by running them within a privacy-ensuring sandbox, hence also facilitating developer’s efforts to intelligently integrate health data. A core concept in the PRECIOUS system is to operate under a common motivational umbrella guided by principles of motivational interviewing (MI) [13] in order to ensure long-term behavior change.

## Methods

### Objectives

The main goal of this pilot study is to assess users’ overall satisfaction, usability, and acceptability of the PRECIOUS system and to explore if MI is a feasible solution to foster adherence to PRECIOUS in a sample of end users. Moreover, we explore whether it triggers behavior change and builds up motivation to maintain sustained change towards healthy lifestyles.

### Hypothesis

Since this is a pilot study aimed at testing the feasibility of using the technology to achieve behavior change, no specific hypotheses have been put forward. Based on previous research on the efficacy of lifestyle apps and MI studies to foster behavior change [9,13-15], it can be expected that intervention groups (Groups 2 & 3) will show a tendency of change towards a healthier lifestyle compared to control group. These changes can be measured with the weight management questionnaires, the substance use/abuse questionnaires, and with several items related to the assessment of one of the main variables of the study (effectiveness).

No preliminary hypotheses have been established about possible differences between intervention Groups 2 and 3. Ideally, both groups will follow PRECIOUS recommendations with no significant differences between them. Thus, the potential benefits of the PRECIOUS app are expected to be achieved without the need for additional support (MI counseling). The PRECIOUS app’s continuous monitoring and feedback, as well as psycho-educational content and messages, are expected to effectively foster healthier lifestyles.

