#### Primary Outcome Measures

To explore users’ acceptance of PRECIOUS system, the following aspects will be assessed:

Usability: 11-item questionnaire (10 items with 5-point Likert scale and 1 item with 10-point Likert scale) to assess users’ interaction with app and system interface.

Satisfaction: 14-item questionnaire (10-point Likert scale) to assess satisfaction with the different modules of the app (physical activity, diet diary), reports, feedback messages, and other interface elements.

Acceptance: 4-item questionnaire (10-point Likert scale) to measure the disposition to use and recommend the system to other patients.

Effectiveness: 15-item questionnaire (10-point Likert scale) to assess engagement, change, and adherence to healthy habits.

In Group 1 (control, treatment as usual), all these aspects will be assessed but with an adaptation of the same questionnaires based on their specific follow-up and the use of the Bodyguard2.

These measures were developed ad hoc for this study, but the usability items are based on the System Usability Scale [16] and acceptance and satisfaction items are based on the Questionnaire for User Interaction Satisfaction 7.0 [17].

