### Statistical Plan

The statistical analysis will consist of intergroup (Groups 2 and 3) descriptive and mean comparison analyses concerning primary outcome measures (usability, user satisfaction, acceptance, and system effectiveness) and overall assessment of the motivational aspects of PRECIOUS. In our pilot test, the method to assess minimal clinically important difference will be employed (distribution-based method, ie, ±1 mean standard deviation) to study differences between groups related to the main primary outcomes [30].

Secondary analyses will describe and explore changes between groups (inter and intra) in the following secondary outcome measures: (1) health-related quality of life using SF12v2), (2) weight management using S-Weight & P-Weight, (3) severity of the core symptoms of depression, anxiety, and stress using DASS, (4) alcohol consumption using Alcohol Use Disorders Identification test, (5) tobacco use with the Fagerstrom Test for Nicotine Dependence, and (6) sleep quality using the Pittsburgh Quality of Sleep Index. For these purposes, correlational, median comparisons, and nonparametric tests (chi-square tests, Mann-Whitney U) will be performed.

Setting the pilot trial sample size in order to minimize overall size has been based on the Kieser and Wassmer approach. They applied the 80% upper control limit approach to sample size calculation and found that a pilot trial sample size between 20 and 40 would minimize the overall sample size for a main study sample size of 80-250, corresponding to standardized effect sizes of 0.4 and 0.7 (for 90% power based on a standard sample size calculation) [31].

All analyses will be carried out using the Statistical Package for Social Sciences, version 19. A 95% confidence interval will be used for all analyses.

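### The article links an expected non-significant Group 2 v Group 3 result to MI being unnecessary, which 10 patients per arm cannot show, and it names no app-use measure for its aim of adherence to PRECIOUS

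*Protocol article*

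**What the plan says.** The Hypothesis section of the protocol article first disclaims any hypothesis on this contrast: "No preliminary hypotheses have been established about possible differences between intervention Groups 2 and 3". It then describes the hoped-for result: "Ideally, both groups will follow PRECIOUS recommendations with no significant differences between them". The following sentence opens with *Thus* and says that "the potential benefits of the PRECIOUS app are expected to be achieved without the need for additional support (MI counseling".

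The Statistical Plan makes this contrast the one named for the primary outcomes: "The statistical analysis will consist of intergroup (Groups 2 and 3) descriptive and mean comparison analyses concerning primary outcome measures". It adds a distribution-based threshold of ±1 SD for an important difference between groups on those outcomes, and states that "A 95% confidence interval will be used for all analyses". It gives no equivalence or non-inferiority margin. Table 1 shows 10 patients in each of Groups 2 and 3.

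The Objectives, repeated under Principal Considerations, include an aim to "explore if MI is a feasible solution to foster adherence to PRECIOUS in a sample of end users". The primary measures are usability, satisfaction, acceptance and effectiveness. Only the last mentions adherence; it is a "15-item questionnaire (10-point Likert scale) to assess engagement, change, and adherence to healthy habits".

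**The concern.** The absence of a significant difference is not evidence of no difference, least of all with 10 patients per arm. If the Hypothesis wording carries over into the report, a moderate and useful effect of MI could go undetected and the null result be read as support for the app alone. The wording also pulls against the Objectives: one looks for an effect of MI on adherence, the other hopes to see no difference.

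The second part concerns what is measured. Whether MI fosters adherence to the system is a question about use of the app. Self-rated adherence to healthy habits is a different quantity, because a patient can change habits without the app or use the app without changing habits. The article's own motivation is that most health apps are abandoned within 3 months, so use over the 3-month study is central to it.

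**Working it through.** **Inputs.** n = 10 and 10 (Table 1). Comparison of means, 95% CI, importance threshold 1 SD (Statistical Plan). The 95% level is read as two-sided 5%; the article does not state sidedness. It gives no SD for the primary questionnaires, so everything is in units of one common within-group SD. No dropout is assumed.

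**1. The article's own sample-size figure.** The only one is a main-study total of 80 to 250 for standardized effects of 0.7 and 0.4 at 90% power. With n per arm = 2(1.960 + 1.282)²/d²:

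- d = 0.7: 42.9, so 43 per arm and 86 in total
- d = 0.4: 131.3, so 132 per arm and 264 in total

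Working back, totals of 80 and 250 imply d = 3.2415·√(2/40) = 0.72 and 3.2415·√(2/125) = 0.41. The quoted range is therefore a rounded one. It concerns a later main study, and nothing below depends on it. No power is stated for Group 2 v Group 3.

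**2. Precision.** Half-width of the 95% CI = t(0.975, 18)·√(2/10) = 2.101 × 0.447 = 0.94 SD. Put differently, an observed difference smaller than about 0.94 SD is non-significant.

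**3. Chance of a non-significant result when MI works.** Two-sided 5% t-test, noncentral t with 18 df and noncentrality d/√0.2:

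| True effect (SD) | Power | Non-significant |
|---|---|---|
| 0.4 | 13.5% | 86.5% |
| 0.5 | 18.5% | 81.5% |
| 0.7 | 31.7% | 68.3% |
| 1.0 | 56.2% | 43.8% |

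80% power needs a true effect of 1.32 SD. A Mann-Whitney test gives slightly less power: about 11%, 28% and 51% at 0.4, 0.7 and 1.0 SD (simulation).

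**4. Chance of showing similarity when the arms are truly equal.** In 200,000 simulated trials the 95% CI lay wholly inside ±1 SD in 18%, and inside ±0.7 SD in 0.7%. With a half-width of 0.94 SD, the observed difference must be below about 1 − 0.94 = 0.06 SD in size to fit within ±1 SD.

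**5. The one-sided question.** To say that MI is not needed, only a benefit of MI has to be excluded. If the arms are truly equal, the upper limit for Group 3 minus Group 2 falls below 1 SD in 56% of trials (noncentrality 1/√0.2 = 2.24). If MI truly gives 0.5 SD, the gap to the threshold is 1 − 0.5 = 0.5 SD and the chance is about 18%. By the normal-approximation formula, excluding a 1 SD benefit with 80% or 90% power under equality would need 16 or 22 per arm.

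**6. Aim against outcomes.** The Objectives name adherence to PRECIOUS. Primary Outcome Measures cover self-rated engagement, change and adherence to healthy habits, and, under acceptance, the disposition to use the system. Secondary Outcome Measures list app-recorded steps and the meal diary as measures of activity and diet, not of use. The secondary outcomes enumerated in the Statistical Plan include neither. No log-in, days-used or retention measure is named.

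**The case against.** The strongest reply is that the article sets no rule. It disclaims hypotheses for this contrast, the key sentence begins with an ideal, the next states an expectation, and the one after gives reasons for it in the app's monitoring, feedback and content. That stands. A reader might infer that the plan commits the authors to declaring MI unnecessary after a null result; the text does not say so. What remains is the link made by *Thus*, and the lack of any statement on how a null result will be read.

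Second, the Statistical Plan already promises 95% CIs and an importance threshold. That also stands, and it makes the repair easier. But the threshold is not described as a margin for concluding that the groups are alike.

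Third, low power is normal in a pilot sized to inform a later study, and at a true effect of 1 SD a significant result is slightly more likely than not (56%). Both are right. The small size is not the fault, and non-significance is the more likely outcome only for effects somewhat below 1 SD.

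Fourth, a reader might infer that adherence is not measured at all. That goes too far: the effectiveness questionnaire touches on engagement, the plan includes an assessment of motivational aspects, and the item wording, Figure 2 and the appendix are not shown. The supportable statement is that the visible text names no app-use outcome for an aim that it states explicitly.

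**Conclusion.** The point holds as a matter of inference and of matching an endpoint to an aim. It should be corrected, but it does not undermine the pilot. A non-significant Group 2 v Group 3 result would be expected about 68% of the time with a true MI effect of 0.7 SD and about 44% with 1 SD, so it cannot show that MI is unnecessary. Even with truly equal arms, the data would confine the difference to within ±1 SD in only about 18% of trials.

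These figures assume roughly normal scores with equal variances, a threshold of one true within-group SD and complete data on all 20 patients; any dropout widens the interval. The margins below 1 SD are illustrations, not figures from the article. The adherence part rests on the visible outcome list only.

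**What to change.** 1. In the Hypothesis section, remove the step from no significant difference to no need for MI. In the Statistical Plan, state that the Group 3 minus Group 2 difference will be reported with the 95% CI already planned. MI will be described as not needed only if that CI excludes a benefit of MI as large as the article's own 1 SD threshold; otherwise the result is inconclusive. Since 1 SD is a large effect, the report should also say that excluding it does not rule out a moderate benefit.

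2. Name an app-use measure for the adherence aim, for example the number of days over the 12 weeks with a meal-diary entry or a manually entered activity. Passive step counts are less suitable, because they may reflect only that the phone was carried.

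The first change is wording; its price is that the conclusion on MI will more often be inconclusive. The second needs diary and manual-entry data to be extractable by patient and day, which the article does not state and is assumed here. Recruitment is complete and results are still pending in the article, so both changes can be made without affecting the conduct of the study.

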### Sample, Recruitment, and Study Design

A convenience sample (non-probabilistic) of patients has been recruited from a specialist outpatient consultation (anonymized for peer review). From an initial list of 55 potential participants, 24 (43.6%) were not included in the study because they were not interested or able to follow the full 3-month protocol. A total of 31 patients (71%, 22 women and 29%, 9 men) meeting the following inclusion criteria has been recruited: (1) patients under the care of medical specialists who adhere to national guidelines for morbid obesity and prediabetic condition following the American Diabetes Association criteria of fasting plasma glucose level from 5.6mmol/L (100 mg/dL) to 6.9mmol/L (125 mg/dL), (2) ˃18 years old, (3) body mass index ≥30, (4) understand and complete questionnaires in Spanish language, (5) use multimedia platforms such as personal digital assistants, tablets, laptops, mobile phones, or personal computers on a regular basis, and (6) have Android devices with an Internet connection. The rationale for choosing participants with Android devices is mainly technical because at this stage of the project, only an Android version of the app is available. Patients with the following criteria have been excluded from the study: (1) any mental (eg, cognitive impairment, severe psychopathology not stabilized) or physical condition that could interfere with the successful application of the research protocol, and (2) technological illiteracy or any other condition precluding the use of a mobile phone. Table 1 shows the demographic characteristics of the sample. Potential participants have been invited to take part in the study via telephone contact and have been randomly assigned into three groups:

Group 1: Control group (treatment as usual + Bodyguard2)Group 2: PRECIOUS system (PRECIOUS app + Bodyguard2)Group 3: PRECIOUS system (PRECIOUS app + Bodyguard2 + MI)

**Table 1 table1:** Demographic and health characteristics of the sample.

Characteristic	Group, mean (SD)			
	1 (n=11)	2 (n=10)	3 (n=10)	Total (n=31)
Age, years	37.45 (11.7)	41.9 (6.2)	38.9 (8.2)	39.35 (9)
Weight, kg	129.18 (17.5)	112.5 (11.7)	116.86 (21.3)	119.83 (18.2)
Height, cm	161.45 (9.3)	165.7 (5.5)	166.9 (9)	164.58 (8.3)
Body mass index, kg/m^2^	49.56 (5.6)	40.9 (2.8)	41.68 (4.4)	44.23 (5.9)
Maximum attained weight, kg	131.36 (19)	117.7 (11.5)	125.2 (20)	124.97 (17.7)
Number of diets last year	3.18 (4.2)	2 (3.2)	2.8 (3.1)	2.68 (3.5)

### Measures

Two types of measures will be registered: (1) A set of primary measures to evaluate users’ opinions and experiences with the PRECIOUS system, and (2) a set of secondary measures to explore the differences between groups across the sessions.

